### Impact of mental resources on language production

Producing a spoken sentence that is linked to previous context and listeners’ expectations involves a number of cognitively demanding mental operations related to language planning for production. The production models posit that planning for production proceeds in three stages: conceptualization, linguistic encoding (i.e., formulation) and phonological encoding (i.e., articulation) [22–25]. By rapidly shifting between these stages, speakers convert the intended meaning (message) into abstract-lexical representations (e.g., lemmas), assign syntactic functions appropriate for the message and order the constituents, given the discourse and grammatical constraints. Finally, the stage of phonological encoding activates the word forms and initiates the motor programming in terms of syllable scores for speaking. In other words, psycho-linguistic study of language production has demonstrated that before starting to speak, speakers process linguistic information in different processing stages or mental modules corresponding to the levels of linguistic analysis (phonological, morphological, syntactic and semantic levels) [24, 26–28].

The existing studies of the relationship between the language production and mental resources in terms of WM indicate that limited mental resources influence the three planning stages to varying degrees [14, 15, 29–32]. These studies usually employ dual-task settings, in which speakers are asked to describe pictures and simultaneously remember a list of words, digits or patterns of squares [14, 15, 29–32]. The dual-task design relies on the notion of cognitive load, or the mental effort arising from splitting one’s attention between the two similar tasks [15, 33]. The underlying assumption is that a very similar secondary task will interfere with the main task and hinder the speakers’ linguistic performance (see also discussions in [15, 33]). The effect of interference as approximated by speech onset latencies and error rates is taken to indicate the involvement of WM in language planning for production. The detrimental effect of cognitive load typically means that planning for production becomes more incremental. This means that language chunks devised prior to articulation are rather small, possibly comprising only the first part of a sentence (e.g., ‘A man’ in the sentence ‘A man is pulling a donkey’) [18, 19, 34–38].

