For linguistic scoring, all sentences will be tagged for a number of linguistic parameters including the syntactic structure, number of actors mentioned, names of the actors, correspondence to the intended actors and mentions of any additional noun phrases or sentence modifiers. In addition, the length of sentences and syllable scores of sentence constituents and actor names are extracted from the phonetic annotations contained in the TextGrids.

A number of exclusion criteria are defined based on the eye movements, linguistic parameters, speech onset latencies and the accuracy of the verb probe task. These exclusions are necessary for the comparability between the sentences because the conceptual planning processes during language production are tightly related to speech timing and the syntactic structures employed. Therefore, target trials will be excluded when the first fixation to the AOI occurs later than 400 ms after picture onset, or when the time delay between the two consecutive fixations is longer than 600 ms (indication of track loss). Picture descriptions of a subject will be included only when (s)he is able to remember at least one word correctly in 90% of the load trials. The final analyses will only include fluent transitive sentences. After these exclusions, additional trials will be excluded based on speech onset latencies later than three standard deviations above the grand mean. Finally, all the data from the subject will be removed when the subject’s inclusion rate after the indicated exclusions is lower than 25%. No treatment of missing data is necessary because the planned regression modelling method (LMER) [82–84] is robust to unbalanced data.

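### Tolerance of unbalanced data does not justify ignoring trial exclusions that are made on behaviour measured after the load manipulation

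*Protocol article*

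**What the plan says.** The section on pre-processing and data harvesting sets the exclusions in sequence.

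- Gaze: "target trials will be excluded when the first fixation to the AOI occurs later than 400 ms after picture onset", and also when more than 600 ms passes between consecutive fixations, which is read as track loss. Neither rule is limited to the gaze outcomes.
- Recall, at subject level: a speaker is kept only if able to "remember at least one word correctly in 90% of the load trials".
- Fluency and structure: "The final analyses will only include fluent transitive sentences".
- Latency: "additional trials will be excluded based on speech onset latencies later than three standard deviations above the grand mean".
- Inclusion rate, at subject level: all data of a speaker are dropped when the "inclusion rate after the indicated exclusions is lower than 25" per cent.

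The section closes with "No treatment of missing data is necessary because the planned regression modelling method (LMER" approach tolerates imbalance. Earlier, under the impact of mental resources on language production, the article says of dual-task studies: "The effect of interference as approximated by speech onset latencies and error rates is taken to indicate the involvement of WM in language planning". The statistical analysis section lists the model terms: Load x Length, block and trial number, and random effects for items and subjects. There is no term for fluency, latency or the chance of being included.

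**The concern.** Robustness to imbalance is a real property of these models, but it answers a different question. It means that unequal numbers per cell do not break the fit. It does not mean that the trials left in each cell represent those removed. For that, exclusion must be unrelated to the outcome given what the model contains.

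The article gives grounds to doubt this on both sides. Load is expected to affect latency and errors, so retention may differ by load. The article also ties conceptual planning closely to speech timing and syntactic structure, and planning is what the gaze outcomes are meant to measure and what is proposed to drive the F0 peaks. Latency is, in addition, the denominator of the proportional gaze outcome. If both links hold, the two load conditions are compared on differently selected trials, and the planned test of Load x Length on sentence-initial peaks inherits the problem.

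A smaller matter concerns precision. The F0 models contain no gaze variable, yet a trial with a lost eye track and a perfectly measurable pitch peak is discarded from them.

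**Working it through.** **1. Which criteria can differ by load.** Four trial-level criteria (first fixation, track loss, fluent transitive sentence, latency) are recorded after load has been imposed. For latency and errors, the article itself states the link to load. For disfluency and the 400/600 ms fixation rules, the link is a reasonable inference and is not stated. The two subject-level rules remove a speaker from both load conditions, so they change who is studied rather than which trials are compared within a speaker.

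**2. Illustrative size for the load main effect.** The article gives no exclusion rate by condition, so all inputs here are assumptions. Suppose a trial is kept when a latent difficulty falls below a threshold, a proportion p is kept, and difficulty correlates r with the outcome. The shift in the mean of kept trials, in outcome SDs, is r x lambda(p), with lambda(p) = phi(z_p)/p. The bias in the load contrast is r x [lambda(p_high) - lambda(p_low)].

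- lambda(0.8) = 0.2800/0.8 = 0.350
- lambda(0.7) = 0.3477/0.7 = 0.497
- lambda(0.6) = 0.3863/0.6 = 0.644

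| Kept, low / high load | Difference in lambda | r = 0.2 | r = 0.5 |
|---|---|---|---|
| 80% / 70% | 0.147 | 0.029 | 0.073 |
| 80% / 60% | 0.294 | 0.059 | 0.147 |

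Set against the planning effect d = 0.45, this is 0.029/0.45 = 7% to 0.147/0.45 = 33%. The sign of the bias follows the sign of r.

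**3. Both links are needed.** Simulation used 84 subjects x 64 trials, 32 per load, with no true load effect, and tested the within-subject load contrast at 5%.

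| Exclusion | Excluded, low / high | Bias (SD) | Rejections |
|---|---|---|---|
| Differs by load, unrelated to outcome | 25% / 43% | about 0 | 6% |
| Related to outcome, same in both loads | 29% / 28% | about 0 | 3.5% |
| Both | 28-34% / 44-45% | -0.04 to -0.07 | 20-48% |

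The first row is the case that robustness to imbalance covers. The third is the case it does not. When a true load effect was instead made to work through difficulty, the estimate on kept trials shrank by 14-18% under moderate selection (31% against 37-41% excluded) and by 34-38% under strong selection (36% against 45-51%). The same mechanism can thus create an effect or reduce one.

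**4. The latency cut alone.** Assume a log-normal latency with median 1800 ms, log-SD 0.3-0.4, and onsets 10-20% slower under load. The 3 SD cut around the pooled mean then removes 0.3-0.9% of low-load and 1.4-2.0% of high-load trials. That is a small part of the problem.

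**5. Not computed.** The bias in Load x Length is a difference of differences. It needs assumed inclusion rates in all four cells, and no figure is offered for it.

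**The case against.** Several points on the other side are sound.

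- A reader might infer that the exclusions work toward hiding the load effect. The article does not support a direction. It says highly incremental speakers may start speaking early, and it expects load to make speakers save time on conceptual decisions, so the latency cut could fall on low-load trials. For F0 peaks it predicts opposing forces: incrementality lowers them and load raises them.
- A reader might also infer that the article names disfluency as a sign of load interference. It names latencies and error rates, in describing earlier studies.
- The sizes above are close to an upper range, because the formula treats all exclusion as a threshold on one variable tied to the outcome. Some track loss will be unrelated to it.
- The exclusions are not arbitrary. The article defends them on comparability of planning across sentences, and a common trial set for gaze and F0 has some interpretive appeal. Restricting to fluent transitive sentences is a legitimate target, provided the result is read as conditional on it.
- Adding disfluent sentences to the F0 model brings in pauses. The article reports that pausing changed the length-pitch relation in earlier read-speech work, so a changed result could reflect phrasing.
- Inclusion tables and sensitivity runs are often left to a fuller analysis plan.

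These points limit the claim about size and direction and shape the remedy. They do not rescue the stated reason, which is an incorrect statement and not an omission. The allowance of about 33% for unusable trials protects precision, not comparability between conditions.

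**Conclusion.** The justification for ignoring missing data is wrong and should be corrected. The Load and Load x Length estimates may be biased by differential exclusion, but neither direction nor size can be determined from the article. The illustrative 0.03-0.15 SD applies to the load main effect only, and rests on assumed inclusion of 80% against 60-70% and an assumed correlation of 0.2-0.5. A demonstrated bias in the main F0 test is not established. Applying the track-loss rule to the F0 models discards usable trials without statistical need, since those models use no gaze variable. This is worth fixing before the data are analysed because the check is cheap and bears on the study's central interaction.

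**What to change.** 1. Replace the sentence. State that LMER accommodates unequal cell counts, that the estimates are conditional on the included (fluent, transitive, timely) trials, and that they assume exclusion is ignorable given the model.
2. Apply the fixation-based exclusions, at least the 600 ms track-loss rule, only to the gaze outcomes. An F0 run on the common trial set can be kept as a check.
3. Keep the fluent transitive set as primary. Report inclusion by Load x Length (and by Double Actor) with a mixed logistic model. Repeat the F0-peak model with late-onset trials and with disfluent transitive sentences that have a measurable first peak, flagging or adjusting for pauses. State whether the Load x Length conclusion holds.

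Trimming latencies within subject and load condition is not a good substitute for the pooled cut. A subject may be kept with 25% of 64 = 16 trials, about 8 per load if evenly spread. The largest possible z-score among n values is (n - 1)/sqrt(n), which is 7/2.83 = 2.47 for n = 8, so a 3 SD rule could never exclude anything there.

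The cost is revised wording, one logistic model and one or two extra runs. Disfluencies and syntactic structure are already to be scored for every description. The downside is slightly different trial sets for the gaze and F0 models.

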#### Dependent variables

The dependent variables of interest are (i) speech onset latencies, (ii) duration of naming gazes, (iii) duration of naming gazes proportional to their respective speech onset latencies, (iv) the height of sentence-initial pitch peaks as indexed by F0 maxima (v) and the height of sentence-final pitch valleys as indexed by F0 minima.

First, the starts of utterances (in milliseconds) index the speech onset latencies. Second, a gaze is defined as multiple consecutive fixations directed at the AOI [72]. Gaze duration is calculated by subtracting the onset time of the first fixation directed at the AOI from the offset time of the last consecutive fixation directed to the AOI. Typically, before the speech onset, between one and five gazes occur (see Fig 5). The number of gazes usually increases together with the complexity of the visual scene. The data analysis algorithm will compare between the durations of the gazes occurring before the speech onsets and determine the gaze with the maximum duration, i.e., the longest gaze. The naming gaze is reported as missing (NA) when, in the very unlikely case of only one gaze or of two gazes of exactly the same duration, the algorithm cannot detect a gaze with the maximum duration. The longest gaze before the speech onset is called the naming gaze and submitted to further analyses together with its AOI (either agent or patient).

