The eye movements in the existing studies are typically investigated as continuously changing functions of time in a fixed time window (from 0 to 400/600/1000 ms of picture presentation) [16–21, 69, 70]. For the purposes of this study, we derive a new relative measure from the eye movements based on what is currently known about eye movement in the linguistic task settings [16–21, 25, 69, 70]. The new metric is based on the notion of gaze that is defined as multiple consecutive fixations directed towards the region of interest [72]. As the clear start of phonological processing is indexed by a long and intense gaze towards the first-mentioned actor/object right before the onset of speech, the new measure takes this long, “naming” gaze as a landmark for the time window between the picture onset and the start of an utterance. In other words, the duration of these naming gazes will be divided by the speech onset latencies based on the following reasoning.

Namely, the time before the naming gaze indexes the time window where the conceptual frame of an incipient sentence is generated. The time after this longest gaze indicates encoding of further aspects of the incipient sentence (possibly the verb or second-mentioned actor). The highly incremental processing entails that after the picture onset, speakers start to encode the first-mentioned actors as soon as possible [18, 36, 69]. Since they might also start their speech early, they may spend most of the time period between the picture onset and the start of an utterance with processing the first-mentioned actors. In other words, the duration of the naming gaze at the first-mentioned actor relative to the speech onset latency is comparably high. Conversely, the weakly incremental planning assumes that speakers also take time for processing second-mentioned actors, such that the naming gaze at the first-mentioned actor starts later [16, 19] and the speech onset may be somewhat delayed. This means that the duration of the longest gaze towards the first-mentioned actor relative to the speech onset latency is rather low. Consequently, the degree of incrementality and the effect of cognitive load on conceptual processing can be inferred from the duration of the naming gaze measured proportionally to the speech onset latency. In particular, the increasing proportional duration of the naming gaze at the first-mentioned actor or object approximates the increase of incrementality in the conceptual planning processes.

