### Data analytic plan and proposed analyses

#### Pre-processing and data harvesting

First, starts and ends of utterances will be detected automatically based on the energy levels in the recorded signals. All of the starts and ends are then manually checked in the phonetic analysis software Praat [80], Together with this checking procedure, all descriptions will be manually transcribed and scored for disfluencies (restarts, corrections, hesitations, breaks) and for employed syntactic structures (e.g., transitive, intransitive, truncated passive). Based on these transcriptions, onsets and offsets of word labels are then determined with the help of the forced alignment tool provided by the Bavarian Archive for Speech Signals (BAS) [81]. The automatic annotation of speech segments is again manually checked with special attention to silent and filled pauses, as they determine the boundaries of prosodic phrases. Finally, all this information is created and stored for each sentence in the TextGrid format provided in Praat. Most importantly, the start of utterances will serve as the measure of speech onset latencies.

F0 of each sentence (in hertz) is extracted with the help of the autocorrelation method available in Praat in two passes. During the first pass, F0 tracks are extracted with default settings for the lowest and highest F0, the “floor” and “ceiling” (75 Hz and 600 Hz, respectively). Then, the first and third quartiles of F0 (Q1 and Q3) are calculated for each speaker and recorded in a table. In the second pass, F0 contours are extracted with speaker-specific settings (0.75*Q1 for floor and 1.5*Q3 for ceiling). The F0 samples making up a contour are saved in the two-column format where the first column contains timestamps and the second column F0 measures at given times.

The timing and position of eye fixations is recorded relative to the regions of depicted actors, the so-called areas of interest (AOI). The AOIs are determined on the basis of the thematic roles. This means that AOIs are defined to cover the areas of agents and patients such that the actors sharing a thematic role are enclosed into a single AOI.

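### A gaze is defined as multiple fixations, so a one-fixation look does not count; with the sole-gaze rule this can set the naming gaze to missing in scan-then-name trials

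*Protocol article*

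**What the plan says.** The definition appears twice. In the introduction (Theoretical assumptions of the new measure of cognitive difficulty) the new metric rests on "the notion of gaze that is defined as multiple consecutive fixations directed towards the region of interest". In Dependent variables it is repeated as "a gaze is defined as multiple consecutive fixations directed at the AOI". Nothing in the article says that one fixation on an area of interest (AOI) also counts.

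Dependent variables then adds four things:
- On gaze duration, the formula is "subtracting the onset time of the first fixation directed at the AOI from the offset time of the last consecutive fixation directed to the AOI". This sets no minimum number of fixations.
- On the expected count: "Typically, before the speech onset, between one and five gazes occur".
- On selection: "The longest gaze before the speech onset is called the naming gaze".
- The naming gaze is recorded as missing (NA) "in the very unlikely case of only one gaze or of two gazes of exactly the same duration".

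Under Statistical analysis, naming-gaze duration and its proportion of speech onset latency are two of the four modelled outcomes. The proportional measure tests whether the verb probe task loaded conceptual planning. Under Pre-processing and data harvesting, missing data get no treatment, on the ground that the mixed model tolerates imbalance.

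**The concern.** The introduction describes attention as split between the actors' regions in roughly the first 400 to 600 ms, followed by a long look at the actor to be named. If each of two early looks had to contain two fixations, four fixations would have to fit into 600 ms, or at most 600 / 4 = 150 ms each before any time for eye movements. If fixations last longer than that (the article gives no durations), at least one early look is a single fixation. Where both are, the trial contains exactly one gaze in the literal sense, and the NA rule removes it.

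The written definition therefore conflicts with the statement that a sole gaze is very unlikely. It also fits poorly with a duration formula that works unchanged for one fixation. Two analysts, one following the words and one following the evident intent, would derive different outcome data from the same recordings. Because loss would depend on the gaze pattern, it may be related to the outcome, and tolerance of unbalanced data does not by itself answer that.

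**Working it through.** **No figure to reproduce.** The article gives no rate of single-fixation looks or of missing naming gazes, so the size can only be shown as a range under assumptions.

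**Two invented records, for illustration.**
- A: agent, one fixation of 230 ms; patient, one of 250 ms; agent, three fixations spanning 900 ms; speech. Counting every look gives three gazes and a naming gaze of 900 ms. The literal rule finds one gaze and returns NA.
- B: agent, one fixation of 600 ms; patient, two spanning 440 ms; agent, two spanning 400 ms. The literal rule picks the 440 ms patient gaze and passes over the 600 ms agent look.

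**Missing share, calculation 1.** Assume k looks before speech, each a single fixation with probability s, independently. Ignoring exact ties:
- literal definition with the sole-gaze rule: P(NA | k) = s^k + k(1 − s)s^(k−1)
- literal definition, sole gaze kept: P(NA | k) = s^k
- one-fixation looks count, sole-gaze rule retained: NA only if k = 1

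Example with s = 0.2 and k uniform on 2 to 5:
- k = 2: 0.04 + 2 × 0.8 × 0.2 = 0.360
- k = 3: 0.008 + 3 × 0.8 × 0.04 = 0.104
- k = 4: 0.0016 + 4 × 0.8 × 0.008 = 0.0272
- k = 5: 0.00032 + 5 × 0.8 × 0.0016 = 0.0067
- mean: 0.498 / 4 = 12.4%
- with a sole gaze kept: (0.04 + 0.008 + 0.0016 + 0.00032) / 4 = 1.2%

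| Assumed k | s = 0.05 | 0.1 | 0.2 | 0.3 | 0.5 | If one-fixation looks count |
|---|---|---|---|---|---|---|
| uniform 2–5 | 2.6% | 5.6% | 12.4% | 21.0% | 43.8% | 0% |
| mostly 2–3 | 9.2% | 13.6% | 23.5% | 34.4% | 58.1% | 5% |
| uniform 1–5 | 22.1% | 24.4% | 30.0% | 36.8% | 55.0% | 20% |

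The row for mostly 2–3 uses weights 0.05, 0.40, 0.35, 0.15 and 0.05 for k = 1 to 5. With a sole gaze kept, the literal definition alone gives 0.1% to 19.4% over the whole grid, and at most 8.6% for s up to 0.3.

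**Missing share, calculation 2.** A simulation of fixation sequences assumed fixations of mean 250 ms (SD 110 ms), 40 ms saccades, a first AOI fixation at 250 ms, mean speech onset at 1600 to 2400 ms, and a probability of 0.4 to 0.7 of staying on the same AOI. At 2000 ms and 0.5, 50.0% of trials had one literal gaze and 6.5% had none, so 56.5% were NA. If one-fixation looks count, 6.1% had only one gaze. Across settings the NA share reached about 70%.

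**Wrong picks.** Calculation 1, extended with lognormal fixation durations (median 250 ms, log-SD 0.45), gives 0.1% to 1.0% of trials under the written NA rule and 0.2% to 4.3% if a sole gaze is kept. In calculation 2, 1% to 5% of trials with at least one multi-fixation gaze left took the wrong look.

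**The case against.** The strongest reply is that this is loose wording and not a wrong method. The duration formula, the expected count of one to five and the remark about a sole gaze all suggest that the authors mean visits to a region, and harm arises only if the algorithm is coded to the letter. That is a fair reading of intent. But the definition is written twice, is registered before data collection and is to be applied by an algorithm, so the text should say what is meant.

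The next objection is about attribution, and it stands. In the central simulated setting, 50.0 of the 56.5 percentage points become NA only through the sole-gaze rule. With a sole gaze accepted, the literal definition leaves 6.5%, about the same as the 6.1% left by changing the definition alone. The large figures belong to the two rules together.

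A reader might infer that the naming gaze will be missing in many ordinary trials. The article does not support this, because it gives no rate of single-fixation looks. It also states that "the actors sharing a thematic role are enclosed into a single AOI", which favours multi-fixation looks in pictures where two actors share a role, and neither calculation models that or the long look before speech. Record B should not be taken as typical either: a 600 ms fixation lies (600 − 250) / 110 = 3.2 SD above the assumed mean.

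A reader might also infer that the test of the load manipulation is biased. No load contrast was computed, and the direction is unclear. A strictly incremental trial with one look straight at the first-mentioned actor is also NA under the sole-gaze rule, whichever definition is used, so loss may occur at both ends of the incrementality scale.

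**Conclusion.** The point holds in a limited form. As written, the definition excludes one-fixation looks and, together with the sole-gaze rule, can set scan-then-name trials to missing, contrary to the article's own expectation that a sole gaze is very unlikely. The missing share lies anywhere from about 3% to about 70%, depending on assumed values of s, k and fixation timing that the article does not supply. It is sizeable only if single-fixation looks are common (s of roughly 0.2 or more) or looks are few. Wrong picks are uncommon, at about 0.1% to 5% of trials. Loss that follows the gaze pattern may relate to the outcome, but no bias of known size or direction has been shown. Two of the four modelled outcomes are affected. The F0 models, including the Cognitive Load by Sentence Length test on pitch peaks, do not use the naming gaze and are untouched. The change is worth making before data are processed because it costs almost nothing.

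**What to change.** In both places, define a gaze as one or more consecutive fixations on the same AOI, uninterrupted by a fixation elsewhere. Keep the stated duration formula and choose the naming gaze from all such gazes before speech onset. In the same edit, reconcile the sole-gaze NA rule with the statement that one to five gazes are typical. Changing the definition alone still leaves every one-gaze trial missing, and changing the sole-gaze rule alone still leaves trials with no multi-fixation look missing and some wrong picks. After processing, report the number of missing naming gazes by load condition.

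The cost is a few words in the definition, a line in the algorithm and a sentence on sole gazes; no new data are needed. The downside is small: brief one-fixation glances enter the comparison, but they are seldom the longest look.
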